## Abstract

**Background:**

Permanent supportive housing (PSH)—subsidized housing paired with support services such as case management—is a key part of national strategic plans to end homelessness. PSH tenants face high overdose risk due to a confluence of individual and environmental risk factors, yet little research has examined overdose prevention in PSH.

**Methods:**

We describe the protocol for a hybrid type 3 stepped-wedge cluster randomized controlled trial (RCT) of overdose prevention practice implementation in PSH. We adapted evidence-based overdose prevention practices and implementation strategies for PSH using input from stakeholder focus groups. The trial will include 20 PSH buildings (with building size ranging from 20 to over 150 tenants) across New York City and New York’s Capital Region. Buildings will be randomized to one of four 6-month intervention waves during which they will receive a package of implementation support including training in using a PSH Overdose Prevention (POP) Toolkit, time-limited practice facilitation, and learning collaboratives delivered to staff and tenant implementation champions appointed by each building. The primary outcome is building-level fidelity to a defined list of overdose prevention practices. Secondary and exploratory implementation and effectiveness outcomes will be examined using PSH staff and tenant survey questionnaires, and analysis of tenant Medicaid data. We will explore factors related to implementation success, including barriers and facilitators, using qualitative interviews with key stakeholders. The project is being conducted through an academic-community partnership, and an Advisory Board including PSH tenants and other key stakeholders will be engaged in all stages of the project.

**Discussion:**

We describe the protocol for a hybrid type 3 stepped-wedge cluster RCT of overdose prevention practice implementation in PSH. This study will be the first controlled trial of overdose prevention implementation in PSH settings. The research will make a significant impact by testing and informing future implementation strategies to prevent overdose for a population at particularly high risk for overdose mortality. Findings from this PSH-focused research are expected to be broadly applicable to other housing settings and settings serving people experiencing homelessness.

**Trial registration:**

ClinicalTrials.gov, NCT05786222, registered 27 March 2023.

**Supplementary Information:**

The online version contains supplementary material available at 10.1186/s13012-023-01278-z.

Contributions to the literature
• Permanent supportive housing (PSH) is an evidence-based intervention for homelessness and is expanding across the USA. Overdose is a critical issue in PSH, yet overdose prevention in this setting has been sparsely researched.• This manuscript describes the protocol for a stepped-wedge cluster randomized controlled trial of overdose prevention practice implementation in PSH. This trial will be the largest study of overdose prevention implementation in PSH to date.• The study will test an implementation framework and novel implementation strategies in PSH, with potential broad relevance to other housing settings.

## Background

The overdose crisis continues to worsen in the USA, and health disparities related to overdose have widened in recent years [1–4]. Amidst these widening disparities, the connections between social determinants of health and overdose have become increasingly clear. For example, research has shown that homelessness is strongly associated with heightened risk for overdose [5–8].

Permanent supportive housing (PSH)—subsidized housing paired with support services such as case management—is a key part of national strategic plans to end homelessness [9]. PSH is generally targeted to people who have been chronically homeless and have significant health conditions, including substance use disorders and mental illness. Decades of evidence, including multiple RCTs, have proven that PSH is highly effective in durably resolving an individual’s homelessness, including for people with serious mental illness and people who use drugs [10–14]. There are currently 387,305 units of PSH across the USA, a number that has grown consistently in the past 15 years and that continues to grow [9, 15]. PSH is sometimes referred to as “Housing First,” which originated as a specific model, but now is a term often used more generally to describe the approach of placing people into housing without stepwise requirements or prerequisites of sobriety or “stability” of mental illness [16, 17]. The original Housing First model has harm reduction as a core tenet, but currently there is variability regarding the extent to which different PSH agencies embrace harm reduction [18].

While housing is critical to ending homelessness, placement into housing alone may not reduce overdose risk [10]. In fact, emerging evidence suggests relatively high overdose rates in PSH and similar housing settings such as single room occupancies (SROs), likely due to a confluence of individual and environmental risk factors [19–21]. For example, in a 2019 survey of leaders from 49 New York PSH agencies, 63% of agencies reported at least one opioid-involved overdose among their PSH tenants in the past year, and at least 118 tenants were known to have died from an overdose in the past 5 years [20]. PSH leaders completing the survey also identified multiple modifiable gaps related to overdose prevention in PSH [20].

Evidence-based practices for overdose prevention exist but their implementation in PSH has been sparsely studied. In general, integration of harm reduction principles and substance use-related initiatives in PSH settings is variable [22–25]. Limited non-experimental research has examined implementation of “Housing First” principles including harm reduction into PSH [26]. One study suggested that training and practice facilitation positively impacted PSH staff knowledge and attitudes toward harm reduction, and was met with high satisfaction [26]. Researchers in Vancouver, Canada, conducted qualitative research examining overdose risk and selected overdose prevention interventions (overdose response buttons and peer-led naloxone training and distribution) in PSH and SROs [21, 27, 28]. However, overall there is a paucity of high-quality evidence related to harm reduction in PSH [29] and there remains a significant gap in the evidence related to the effective implementation of overdose prevention practices in these settings. Indeed, to our knowledge, there has not yet been any experimental research examining implementation of overdose prevention practices in PSH. We seek to fill this gap by conducting a stepped-wedge cluster RCT to study the implementation of overdose prevention practices across 20 PSH buildings in New York.

## Methods

### Study design

This study is a hybrid type 3 trial using a stepped-wedge cluster RCT design [30], with the primary goal of studying building-level implementation of overdose prevention practices in PSH and a secondary goal of examining effectiveness on clinically relevant tenant outcomes. A stepped-wedge cluster RCT design was chosen because it can provide rigorous evidence for intervention effects while allowing all participating buildings to eventually receive the intervention, in contrast to traditional two-arm RCTs. The stepped-wedge design also presents advantages including feasibility related to staggered intervention start times, and improved power versus parallel cluster RCTs.

The study is funded by the National Institute on Drug Abuse of the National Institutes of Health and was approved by the Institutional Review Board at NYU Grossman School of Medicine. The study’s external Data Safety and Monitoring Board meets twice yearly. This manuscript adheres to CONSORT reporting guidelines for cluster randomized trials (checklist provided as an Additional file 1: Table S1).

### Conceptual frameworks

We drew on the EPIS (Exploration, Preparation, Implementation, Sustainment) framework to guide the study’s design [31, 32]. This multilevel framework includes both process (“phases”) and determinant (“constructs”) components. We previously completed the Exploration phase through surveys conducted with PSH building leaders in New York to identify the scope of overdose and related gaps in PSH [20]. The Preparation phase of our work uses key stakeholder focus groups to refine a package of overdose prevention practices and implementation strategies for PSH. The stepped-wedge cluster RCT encompasses both the implementation and sustainment phases of EPIS, as further described in the sections that follow.

We consider key drivers of overdose risk and overdose prevention practice implementation in PSH within the EPIS constructs of outer context, inner context, bridging factors, and innovation factors. We organize these further within Rhodes’ Risk Environment Framework, which categorizes physical, social, economic, and policy-level risks at the level of the micro- and macro-environment [33]. Researchers have previously used Rhodes’ Risk Environment Framework to categorize environmental factors that confer risk for overdose in SROs, such as lack of shared spaces and rules or norms which may lead to using drugs alone [21, 34, 35]; many of these risks are common to PSH settings. We hypothesize that building receipt of an intervention package that considers the inner and outer context in PSH—as we are developing in the study’s Preparation phase—will improve fit and, subsequently, the likelihood that buildings will successfully implement the overdose prevention practices.

The overall project is grounded in the philosophies of community based participatory research (CBPR) [36]. From the beginning of the project, academic investigators have worked in partnership with the Metro Team (covering New York, New Jersey, and Pennsylvania) of the Corporation for Supportive Housing (CSH). CSH is intimately familiar with strengths, assets, and barriers specific to PSH. In the study’s Preparation phase, the planned overdose prevention practices and implementation strategy package are being refined based on input from PSH leaders, frontline staff, and tenants. Additionally, the project is guided by a Study Advisory Board (SAB) at all stages of the research. The SAB includes PSH tenants and staff, people with lived experience of drug use, and representatives from relevant community (e.g., harm reduction, housing advocacy) and governmental (e.g., city and state departments of health) organizations.

### Setting

The stepped-wedge cluster RCT will include 20 PSH buildings in New York City (NYC) and New York’s Capital Region. These areas were chosen to provide a diversity of settings, enhancing generalizability. New York’s Capital Region encompasses the mid-sized metropolitan areas of Albany, Troy, and Schenectady. This trial includes *congregate* PSH buildings, where PSH tenants live together and have access to onsite social services such as case management. In general, onsite services are provided by a nonprofit agency whose portfolio might include multiple PSH buildings as well as other homeless services. Separate property/building management companies may operate the physical housing/apartment complex. Some congregate PSH buildings are mixed-use buildings, also having affordable or market-rate units for non-PSH tenants. Congregate PSH stands in contrast to “scattered site” PSH, where PSH tenants live “scattered” in subsidized market units across the community. Our trial focuses on congregate PSH because this form of PSH is most amenable to building-level interventions and most generalizable to other types of buildings serving populations at high risk for overdose.

### Study population and eligibility

Twenty PSH buildings in NYC and New York’s Capital Region were selected for participation in the trial. CSH’s Metro Team conducted initial outreach to 57 nonprofit agencies in NYC and the Capital Region that provide PSH services, representing the large majority of such agencies in these areas. Agency leaders were provided with written information about the project. They were also invited to an information session held by Zoom and engaged in individual meetings to discuss the project. Agencies were asked to complete online building assessment questionnaires including questions about the size of the building, population served, number of fatal and nonfatal overdoses in the past year, and existing building practices related to overdose prevention. Questionnaires were completed by 25 agencies, encompassing 44 unique buildings. Of the 32 agencies to whom outreach was conducted who did not ultimately complete a questionnaire, 15 did not reply to outreach e-mails, 8 expressed that they were not interested in the project, and 9 were determined not to be eligible (e.g., due to not providing congregate PSH).

The CSH Metro Team and academic study team used the information gathered from their meetings with buildings and from the building assessment questionnaires to select buildings for participation. The primary selection criteria were that buildings had to have at least 20 PSH tenants and overdose had to be a significant concern, as demonstrated either by report of past overdoses on building assessment questionnaires or report from building leaders during meetings. Of the 44 buildings completing building assessment questionnaires, 2 were not eligible based on size and 2 expressed that they did not want to participate. From the remaining 40 buildings, we selected and invited 20 to participate; 3 buildings (from 2 agencies) declined and were replaced to reach 20 participating buildings. Selection prioritized buildings with high levels of overdose concern. Buildings also had to have some degree of “room to improve” in overdose prevention, as demonstrated by their building assessment questionnaire responses related to existing overdose prevention efforts or based on gaps in overdose prevention identified in meetings. To maximize generalizability, buildings were not required to demonstrate a certain level of readiness for implementing new overdose prevention practices; however, buildings did have to express willingness to engage in activities to support them in implementing new overdose prevention practices (e.g., practice facilitation meetings), and to participate in the research study procedures. We also aimed to ensure diversity in participating buildings (e.g., in population served or agency size). No more than two buildings were selected from any given nonprofit agency and, in the case of multiple buildings from the same agency, buildings were required to be geographically dispersed, have different directors, and operate independently, to avoid concerns related to “clustering.” Larger buildings were prioritized for selection in NYC given that Capital Region buildings tend to be smaller (see “Sample size” and “Power” sections).

Leaders from the 20 buildings participating in the trial completed a project participation agreement with CSH and a data sharing agreement with the academic study team.

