### Randomization

Buildings will be randomly assigned to one of four sequential 6-month intervention waves (five buildings per wave). With the stepped-wedge design, all study buildings will begin in the control condition. Buildings are randomly assigned to cross over at different times, with all eventually receiving the intervention. See Fig. 1 for a schematic of the stepped-wedge cluster RCT design.

Randomization will be conducted by the study statistician, who will not have contact with the PSH buildings. There is no stratification of randomization. Buildings will be notified of their assigned intervention wave before the first wave starts.

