### Statistical analysis

To estimate effects of the intervention on the primary outcome, we will use a linear mixed model that incorporates both within- and between-cluster information and accounts for secular temporal trends. In particular, to assess the intervention effect, we will use a model with random site effects of the form: *Y*_it_ = μ + β_1_t + β_2_I_*it*_ + β_3_I_*it*_(*t* – s_*i*_) + b_*i*_ where *Y*_*it*_ is the fidelity checklist score in building *i* during period t, for t ∈ (0, 1, …, 4). Each period is 6 months; *t* = 0 is the first 6-month period. *I*_it_ is an indicator variable; I_*it*_ = 1 if building *i* has been assigned to implementation at period t and *I*_it_ = 0 otherwise. s is the period when implementation begins for building *i*. b_*i*_ is a random effect associated with each building *i* (the deviation of the intercept for the building from the overall intercept μ). Models will take into account a general time trend and allow for the intervention effects to grow over time following implementation. Models will be fit using the lme4 package using R software. Each hypothesis will be tested using a two-sided level of significance α = 0.05. Similar models will be used for analysis of the secondary implementation outcomes.

Implementation sustainment will be measured in the 8th month after the conclusion of each 6-month intervention wave. Paired-samples *t* tests will be used to compare each building’s fidelity scores at the end of its control period with scores during the sustainment period. For buildings assigned to early waves, there is also an opportunity to measure longer term (> 12 months) sustainment within the study measurement period.

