### Power and sample size

With 20 buildings participating in the study and 4 “steps” or waves in the stepped-wedge RCT (i.e., *n* = 100 observations over time across all buildings given 5 total time points per building), we will have at least 80% power to detect an increase of approximately two-thirds of a standard deviation (*d* = 0.69) or larger in the primary implementation outcome, a meaningful and feasible difference. This assumes a moderate correlation between scores for the same building at different time points (ICC = 0.5), reflecting stable differences among buildings. Even in the unlikely event that we do not retain 20 buildings in the study, with 16 buildings we would still have at least 80% power to detect an increase of about three-quarters of a standard deviation (*d* = 0.77) in the primary implementation outcome. To make these effect sizes more concrete, if the checklist score had a standard deviation of 8 and an average score of 15 under the control condition, the stepped-wedge design has 80% power to detect an increase of about 5 to 6 points on the checklist score (e.g., an increase from 15 to 20).

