## Discussion

We describe the protocol for a hybrid type 3 stepped-wedge RCT of overdose prevention practice implementation in PSH. Changes in the epidemiology of the overdose crisis—including widening racial and ethnic disparities—highlight the necessity of concerted efforts to reduce the disparate burden of overdose faced by structurally marginalized populations. Homelessness and housing instability are strongly associated with increased risk of overdose [5, 7, 8, 61–65]. And, while PSH is an evidence-based intervention to resolve homelessness [13, 66], additional interventions are needed to reduce tenant overdose risk.

The 20 PSH buildings participating in the trial have distinct leadership teams, are geographically disbursed across NYC and in New York’s Capital Region, and are not generally accustomed to participating in research studies. Buildings are heterogenous in size, harm reduction orientation, and existing tenant services. Though these factors increase the complexity of study administration, ultimately, we hope that they enhance the real-world applicability and generalizability of the study. The partnership of academic researchers with the Metro Team of CSH, a national nonprofit organization focused on advancing best practices in PSH, is critical for enhancing the feasibility of the study. As a trusted entity in the field, CSH is well-positioned to deliver the implementation intervention to PSH buildings participating in the study and, eventually, to disseminate the study results nationally. Project planning has also included significant involvement of people with lived experience of drug use and as PSH tenants, which we believe has further enhanced the feasibility and real-world applicability of the study. Other strengths of the trial include the multiple, robust sources of data being used to evaluate implementation and effectiveness outcomes.

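### The primary model uses none of the building-level data collected before randomisation; prespecifying one baseline covariate would give a modest gain in precision

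*Protocol article*

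**What the plan says.** **Baseline data.** Under Study population and eligibility, agencies completed an online questionnaire for each building. It covered building size, population served, "number of fatal and nonfatal overdoses in the past year, and existing building practices related to overdose prevention". The article reports that "Questionnaires were completed by 25 agencies, encompassing 44 unique buildings". The team used what it learned in meetings and "from the building assessment questionnaires to select buildings for participation", and the 20 trial buildings came out of that process. The only use the article states for these answers is selection.

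**Allocation.** The Randomization section assigns five buildings to each of four waves, without stratification.

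**Primary model.** The Statistical analysis section says "we will use a model with random site effects of the form" and then gives the equation: intercept, linear time, an intervention indicator, that indicator multiplied by time since the building's start, and a random building intercept. It contains no building characteristic.

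**Building differences.** The Power and sample size section states: "This assumes a moderate correlation between scores for the same building at different time points (ICC = 0.5), reflecting stable differences among buildings". The Discussion adds: "Buildings are heterogenous in size, harm reduction orientation, and existing tenant services". The Abstract gives "building size ranging from 20 to over 150 tenants".

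**The concern.** In a stepped-wedge trial the intervention estimate combines within-building change with comparisons between buildings that are in different conditions at the same time. The second part carries the stable differences between buildings. If a characteristic known before randomisation predicts the fidelity score, adding it to the model removes part of that variance. It also limits how far a chance imbalance between waves of five can move the estimate.

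Two of the recorded characteristics are plausible predictors. Existing overdose-prevention practices concern the same subject as the fidelity checklist. Size may matter because some practices in Table 2 are meant to reach every tenant, while Table 1 gives each building the same number of champions. The article shows neither association.

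What is at stake is precision. With 20 buildings and a design set at about 80% power, a cheap gain is worth considering. It has to be specified before outcome scores are seen.

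**Working it through.** **Inputs.** From the article: 20 buildings, four waves of five, five time points, ICC 0.5, two-sided α = 0.05, detectable d = 0.69 (0.77 with 16 buildings), illustrative SD of 8 points. Assumed: R², the share of between-building variance that the covariate explains, shown from 0 to 0.8. Wave 1 buildings are taken to be on intervention from t = 1, so the step effect β₂ is the effect at a building's first post-start checklist.

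**Method.** Total variance is set to 1, so τ² = 0.5 between buildings and σ² = 0.5 within. For each building V = τ²J + σ²I, with J a matrix of ones and I the identity. The covariance of the fixed effects is (Σ XᵢᵀV⁻¹Xᵢ)⁻¹. Detectable d = SE × (1.960 + 0.842). Power = Φ(d/SE − 1.960).

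**Step 1: the plan's own figures.**
- 20 buildings, without the growth term: SE 0.2449, detectable d = 0.2449 × 2.802 = 0.686 (stated 0.69).
- 16 buildings: SE 0.2739, d = 0.767 (stated 0.77).
- In points: 0.69 × 8 = 5.5, matching the stated 5 to 6.
- With the growth term, as in the written model: SE 0.2471, d = 0.692, power at 0.69 of 79.7%. This still agrees with the stated figure after rounding.

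**Step 2: how much the written model already removes.** Using within-building information only, the SE of the step effect is 0.2681. Since (0.2471/0.2681)² = 0.85, about 85% of the information on this effect is already free of stable building differences. A covariate that is constant within a building can improve only the rest.

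**Step 3: effect of adjustment on the step effect.** τ² becomes 0.5 × (1 − R²), and one covariate coefficient is estimated from 20 buildings (averaged over random covariate draws; the last digit of power can move by about 0.1).

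| R² | SE, effect known | SE, one estimated | Power at 0.69, one estimated | Detectable d |
|---|---|---|---|---|
| unadjusted | – | 0.2471 | 79.7% | 0.692 |
| 0 | 0.2471 | 0.2480 | 79.4% | 0.695 |
| 0.2 | 0.2440 | 0.2450 | 80.4% | 0.686 |
| 0.5 | 0.2370 | 0.2381 | 82.6% | 0.667 |
| 0.8 | 0.2241 | 0.2255 | 86.4% | 0.632 |

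On the 8-point SD, the detectable effect falls from 5.54 points to 5.49 at R² = 0.2 and 5.34 at R² = 0.5. The R² = 0.5 gain is worth about 20 × [(0.2471/0.2381)² − 1] = 1.5 buildings.

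With two covariates estimated, power is about 79.2%, 80.1%, 82.2% and 86.0% at the same four values of R².

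**Step 4: effect averaged over exposure time.** The model lets the effect grow. Over the four exposure points (0 to 3 periods since start) the average effect is β₂ + 1.5β₃, with unadjusted SE 0.336. With one covariate estimated it is 0.331 at R² = 0.2 (about 2% lower) and 0.313 at R² = 0.5 (about 7% lower). The gain is larger because this contrast relies more on comparisons between buildings.

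**Limits.** Variance components are treated as known and the reference is normal. A t reference with 18 degrees of freedom raises the detectable d to about 0.73 but leaves the relative change in SE as shown.

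**The case against.** The case for leaving the model alone is strong in several respects.

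- **The analysis is valid without adjustment.** Randomisation protects the estimate, and the ICC in the power calculation already counts the between-building variance. A reader might infer that unstratified allocation plus an unadjusted model biases the result, or that the stated power is wrong. The article supports neither: chance imbalance is part of the standard error, and the power figures reproduce.
- **Building differences are not ignored.** A reader might infer that the predictable variance is left wholly unaddressed. It is not. The random intercept spans five scores, including the checklist before wave 1, which is a closer pre-trial reading of the outcome than any questionnaire item. Step 2 puts a figure on this.
- **The covariates may be weak.** The article defines no existing-practices score. The questionnaire is self-reported, whereas the outcome comes from two raters using benchmarked criteria. Selection favoured buildings with scope to improve, which may narrow the range of existing practices. An effect of size is conjecture.
- **Adding everything on hand could cost precision.** With three covariates estimated (same method, without the growth term), the SE is 0.4% higher at R² = 0.10 and only 0.3% lower at R² = 0.25.
- **An unseen analysis plan may add covariates.**

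The first four points stand, and they limit both the size of the concern and the number of covariates worth adding. The last carries less weight, because the article does not leave the primary model open: it writes out the equation, and the comment is on that equation.

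**Conclusion.** The point holds as a minor efficiency improvement. Baseline building data were collected before randomisation, and the written primary model uses none of them. The plan is otherwise sound here: the analysis is valid and the power statement is correct.

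The size depends on R², which the documents do not give. For the step effect, one covariate changes power at d = 0.69 by about −0.3 points at R² = 0, +0.7 at 0.2, +2.9 at 0.5 and +6.7 at 0.8. Nothing in the article supports the top of that range. The gain is somewhat larger for the effect averaged over exposure. It would not be right to conclude that the trial is underpowered without adjustment, or that size, overdose count and existing practices should all go into the model.

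**What to change.** Before any follow-up checklist is scored, add one fixed building-level covariate to the primary model: Y_it = μ + β₁t + β₂I_it + β₃I_it(t − s_i) + γx_i + b_i. Here x_i is a simple count of existing overdose-prevention practices from the selection questionnaire, with the items and their coding written down in advance. Log number of PSH tenants may be added as an optional second covariate. Report the model as now written as a sensitivity analysis. Leave the power and sample size figures unchanged, since they remain valid for the unadjusted model.

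**Cost.** One line in the analysis plan and a short coding rule, because the article defines no such count. It uses one or two between-building degrees of freedom. If the covariates turn out not to be predictive, the loss is under 1 point of power: about 0.3 with one and about 0.5 with two. No new data collection is needed.
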